## Abstract

**Introduction:**

Most cardiac arrest survivors are classified with mild to moderate cognitive impairment; roughly, 50% experience long-term neurocognitive impairment. Postarrest challenges complicate participation in society and are associated with social issues such as failure to resume social activities and impaired return to work. The effectiveness of rehabilitation interventions for out-of-hospital cardiac arrest survivors are sparsely described, but the body of evidence describes high probabilities of survivors not returning to work, returning to jobs with modified job descriptions, returning to part-time employment, and often in combination with extensive unmet rehabilitation needs. Hence, there is a need to develop and test a pragmatic individual targeted intervention to facilitate return to work (RTW) in survivors of OHCA. The overall aim of the ROCK trial is to evaluate the effectiveness of a comprehensive individually tailored multidisciplinary rehabilitation intervention for survivors of OHCA on RTW compared to usual care.

**Methods and analysis:**

The ROCK trial is a two-arm parallel group multicentre investigator-initiated pragmatic randomized controlled superiority trial with primary endpoint measured 12 months after the cardiac arrest. Adult survivors who were part of the labour force prior to the OCHA and had at least 2 years until they are qualified to receive retirement state pensions are eligible for inclusion. Survivors will be randomized 1:1 to usual care group or usual care plus a comprehensive tailored rehabilitation intervention focusing on supporting RTW. After comprehensive assessment of individual rehabilitation needs, the intervention is ongoingly coordinated within a multidisciplinary rehabilitation team, and the intervention can be delivered for up until 12 months. Data for the primary outcome will be obtained from the national register on social transfer payments. The primary outcome will be analysed using logistic regression assessing RTW status at 12 months adjusting for the intervention and age at OHCA, sex, marital status, and occupation prior to OHCA.

**Discussion:**

The ROCK trial is the first RCT to investigate the effectiveness of a rehabilitation intervention focusing on return to work after cardiac arrest.

**Trial registration:**

ClinicalTrials.gov NCT05173740. Registered on May 2018

**Supplementary Information:**

The online version contains supplementary material available at 10.1186/s13063-024-07911-6.

## Background

Each year, more than 5000 citizens experience an out-of-hospital cardiac arrest (OHCA) in Denmark. In 2021, the Danish 30-day survival rate was 13% equivalent to yearly incidence of 610 OCHA survivors [1].

Rehabilitation targeting physical, neurological, and psychological consequence after OHCA is recommended in international clinical guidelines. Due to hypoxic–ischaemic brain injury, the course of acute post-cardiac arrest care and the trauma of resuscitation the frequency of cognitive impairment and emotional reactions are high in survivors of cardiac arrest. These problems affect survivors and restrict their ability to return-to-work (RTW) [2, 3]. Although the majority of cardiac arrest survivors are classified with mild to moderate cognitive impairment, roughly 50% experience long-term neurocognitive impairment. Thus, most cognitive recovery is found to occur during the first 3 months after resuscitation [4, 5]. Looking at emotional issues, both depression, anxiety, and post-traumatic stress disorder are found to affect approximately 20–25% of survivors in the long term [6]. Overall, these neuropsychological postarrest challenges complicate participation in society and are associated with social issues such as failure to resume social activities and impaired RTW [3, 6, 7]. A Danish nationwide cohort study by Jørgensen and colleagues investigated RTW and the subsequent detachment from employment in cardiac populations [8]. The authors found high probabilities of not returning to work, in patients diagnosed with heart failure. These results are in line with our previous findings [2]. Six months after resuscitation, we found 58% of survivors on full-time sick leave or working notable less (10 h/week) compared to prior to the cardiac arrest. In addition, an extensive part of those who had RTW had changed job descriptions or had been assigned less demanding job tasks. Other resuscitation research support these findings, as they found that flexible work hours and/or modified job descriptions were offered to 74% of participants in a register-based OHCA population [9].

Still, the effectiveness of rehabilitation interventions for OHCA survivors are sparsely investigated [10]. Only three randomized controlled studies (393 participants) have been reported; however, none of these reported data on return-to-work. Previously, our research group has evaluated the activity of daily living (ADL) ability of 61 OHCA survivors at discharge from hospital and found that the majority had a rehabilitation potential [11]. In another study, we found that although survivors of OHCA received a variety of postarrest rehabilitation interventions, 45% still reported unmet rehabilitation needs 6 months after their cardiac arrest [2]. This is in line with qualitative findings which emphasize that especially younger cardiac arrest survivors need special attention, as they struggle against impairments and ignore them for a long time in an effort of returning to their previous daily life [12]. Hence, there is a need to develop and test a pragmatic individual-targeted intervention to facilitate RTW in survivors of OHCA.

### Objectives

The overall aim of the ROCK trial is to evaluate the effectiveness of a comprehensive individually tailored multidisciplinary rehabilitation intervention for survivors of OHCA on RTW compared to usual care. We hypothesize that the intervention will result in a higher-level labour marked attachment 1 year after hospital discharge in addition to increased health-related quality of life.

## Methods

### Trial design

The ROCK trial is a two-arm parallel group multicentre investigator-initiated pragmatic randomized controlled superiority trial with primary endpoint measured 12 months after the cardiac arrest.

### Trial sites and recruitment

Cardiac arrest survivors will be recruited from two cardiac arrest centres in the Capital Region of Denmark: Department of Cardiology, Copenhagen University Hospital-Rigshospitalet, and Department of Cardiology, Copenhagen University Hospital-Herlev and Gentofte Hospital.

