### Usual care

All participants including those allocated to the usual care group will be seen by an occupational therapist if their MoCA screening score ≤ 26. Furthermore, if considered relevant by the discharging unit, survivors are referred for rehabilitation provided and delivered in the local municipality where the participant is resident. The content of the rehabilitation will typically be based on the content of the rehabilitation plan from the discharging hospital unit and an individual assessment of the survivors’ expressed needs, within the local municipality where the participant is resident.

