### Strategies to improve adherence

The feasibility of the intervention has been tested and the intervention refined based on the gained experiences. As the study is a pragmatic study based on an individual assessment of the survivors’ expressed needs, the intervention is expected to be relevant for all participants. However, due to the single centre set-up transport to and from the study site could be a limiting factor to adherence. However, financial compensation for transport costs was offered to the participants. Furthermore, the intervention is designed to include relatives, and hence, the acceptability is expected to be relatively high, and relatives are therefore expected to be supportive and thereby increase the possibility of higher adherence to the intervention.

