### Recruitment, assignment of interventions, sequence generation, and allocation concealment

We will recruit trial participants directly from the cardiology ward. A study nurse at the ward will approach eligible survivors and invite them to participate in the present study. Participants will be randomly assigned to either the intervention or the usual care group using a computer random generator, with a 1:1 allocation by using varying block sizes. The randomisation will be conducted using the RedCap randomization module and will be stratified on sex (M/F) and age. Allocation concealment will be ensured as the randomization module block sizes are unknown, and the allocation will be locked after randomization. Clinical staff at the departments will obtain informed consent and enroll the participants. A named study author ([name], [name], or [name]) will randomize participants, and the clinical staff at the departments will inform the participants about the allocation and start the intervention based on standard operating procedures. The CONSORT flow diagram is presented in Fig. 2.

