### Secondary outcomes

Secondary outcomes will be analysed using generalized linear mixed-effects models. Data are measured repeatedly, but outcomes are binary or on ordinal scale. Crude and adjusted analysis will be presented. Covariates that will be adjusted for include age at OHCA, sex, educational level, and marital status. Continuous data will be analysed using *t*-test for normally distributed data and Wilcoxon’s signed-rank test for non-normally distributed data. For categorical data, chi-square test will be used.

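### Recruiting hospital is in neither the randomisation strata nor the stated primary model, although the discharging unit shapes usual care; adding it as a covariate is a minor, cheap improvement

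*Protocol article*

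**What the plan says.** Trial design calls ROCK a "two-arm parallel group multicentre investigator-initiated pragmatic randomized controlled superiority trial". Trial sites and recruitment says that "Cardiac arrest survivors will be recruited from two cardiac arrest centres in the Capital Region of Denmark" and names two cardiology departments.

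The section on recruitment and sequence generation sets randomisation "with a 1:1 allocation by using varying block sizes", which "will be stratified on sex (M/F) and age". Hospital is not a stratum.

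The primary logistic regression is described as "adjusting for the intervention and age at OHCA, sex, marital status, and occupation prior to OHCA". The same covariates appear in the abstract, in the statistical section on the primary outcome, and in the shells of Tables 2 and 3 under Planned reporting. For the secondary mixed models the text is "Covariates that will be adjusted for include age at OHCA, sex, educational level, and marital status". The only subgroup sensitivity analyses, under Definition of analysis, are by type of work.

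Usual care gives the hospital a role in the comparator: "if considered relevant by the discharging unit, survivors are referred for rehabilitation provided and delivered in the local municipality". It adds that the municipal content typically rests on the discharging unit's rehabilitation plan together with an individual assessment in the municipality.

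**The concern.** Hospital is a baseline factor known for every participant, and in the article's own account it influences whether background rehabilitation is arranged and what it contains. Such a factor is usually balanced by design, adjusted for in the model, or both. Here it is neither in the primary analysis as stated.

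This is more than detail left to the statistical analysis plan (SAP). The primary covariate list is fixed in three places, so an SAP that follows the article would omit hospital.

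At stake is conditional balance. If RTW differs between the hospitals after allowing for age, sex, marital status and occupation, and one arm happens to draw more patients from the better hospital, part of that difference enters the realised treatment estimate. Some precision is also lost.

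**Working it through.** **Inputs from the article (Sample size).** RTW 71% under control and 88.8% under intervention; 85 per arm, raised to 107 for 20% dropout. The inflation reproduces: 85 / (1 − 0.20) = 106.25, rounded up to 107. The 85 itself does not follow from the stated 10% margin and 80% power. That is a separate question, and both sizes are taken here as given. The article has no figure on hospital differences to reproduce.

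**Assumptions, not in the article.** Patients split evenly between the hospitals (π = 0.5); hospital gap in RTW of 5, 10 or 20 percentage points.

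**1. Chance imbalance in hospital mix.** The SD of the between-arm difference in hospital share is √(2π(1 − π)/n).
- n = 107: √(0.5/107) = 0.068. The chance of an imbalance of 10 points or more in either direction is about 14%, so about 7% in the direction that favours the intervention.
- n = 85: √(0.5/85) = 0.077, and the chance is about 19%.
- With a 70:30 split the SDs are 0.063 and 0.070.

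**2. Shift in the risk difference.** Shift = imbalance × hospital gap. The 95% range over all randomisations is ±1.96 × SD × gap:

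| Assumed gap | n = 107 | n = 85 |
|---|---|---|
| 5 points | ±0.7 | ±0.75 |
| 10 points | ±1.3 | ±1.5 |
| 20 points | ±2.7 | ±3.0 |

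Among trials with an imbalance of at least 10 points favouring the intervention, simulation at 107 per arm gives an average shift of about 1 point (10-point gap) and 2 to 3 points (20-point gap) without hospital in the model. With hospital in the model the shift is essentially zero.

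**3. Compared with sampling error.** SE = √[(0.71 × 0.29 + 0.888 × 0.112)/n] = √(0.3054/n), which is 5.3 points at n = 107 and 6.0 at n = 85.

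**4. On the odds-ratio scale used in Table 2.** The planned OR is (0.888/0.112)/(0.71/0.29) = 3.24. A 10-point imbalance moves it to between 3.01 and 3.49 (10-point gap), or between 2.80 and 3.77 (20-point gap), depending on direction.

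**5. Operating characteristics.** These come from simulation of the unadjusted two-proportion test, 85 per arm, gaps of 0, 10 and 20 points, no margin. The mean estimate is 0.178 against a true 0.178. Type I error is 0.049 to 0.051 without balancing hospital. Power is 0.844 to 0.847 without balancing and 0.846 to 0.852 with it.

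**6. Precision from adjustment.** With an even split, the hospital gap contributes a variance of 0.25 × gap². At 20 points this is 0.010, or 4.9% of 0.71 × 0.29 = 0.206. At 10 points it is 0.0025, or 1.2%. Simulated variance ratios (adjusted to unadjusted) run from 0.94 to 1.01 across scenarios: up to about 3 to 6% gain at a 20-point gap, practically none at 10, and at most about 1% loss with no gap.

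**7. Room in the model.** Expected participants not back at work: 85 × 0.29 + 85 × 0.112 = 34, or 107 × 0.29 + 107 × 0.112 = 43. The primary model already has at least five coefficients besides the intercept; hospital would make six.

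**The case against.** The strongest reply is that chance imbalance under 1:1 randomisation is not bias and that the confidence interval already carries it. Step 5 bears this out. A reader might infer from the omission that the primary estimate is biased or its test invalid; the documents and the calculations do not support that.

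Nor does the article say that RTW, case mix or referral practice differs between the hospitals. Both are university cardiology departments in one region, and the existing covariates would absorb part of any case-mix difference. The mechanism is also diluted: the municipality of residence delivers the rehabilitation and makes its own assessment. The intervention appears to be delivered at one site, since the adherence section says that "due to the single centre set-up transport to and from the study site could be a limiting factor to adherence". All of this stands, and it limits the size of the point.

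Two further inferences are tempting. First, because Superiority margins requires a difference of 10% or more, a shift of 1 or 2 points might seem able to reverse the conclusion. That needs the 10% to be an absolute risk difference. The section does not say so, and Table 2 reports odds ratios only. Second, the secondary covariates might be read as a complete list that excludes hospital. The wording there is that the covariates include those named, so hospital is merely not mentioned and the SAP could add it. The primary list has no such opening.

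What survives is that the stated primary model leaves out a known design factor with a documented link to the comparator, and that including it costs almost nothing.

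**Conclusion.** The point holds as a minor one. Hospital is absent from the strata and from the stated primary model, and it is not named for the secondary models. The consequence is possible loss of conditional balance and a little precision, not bias over randomisations or an inflated error rate.

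The size depends wholly on an assumed hospital gap and an assumed even split. In the roughly 7% of trials (107 per arm) where the imbalance reaches 10 points in favour of the intervention, the shift is about 1 point for a 10-point gap and 2 to 3 points for a 20-point gap, against a standard error of 5 to 6 points. If the hospitals do not differ, there is no shift.

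**What to change.** Pre-specify recruiting hospital (two levels) as a fixed covariate in the primary logistic regression and add a row for it to Table 2. Name it also among the covariates of the secondary mixed models. Leave the randomisation unchanged: recruitment began in February 2022, and the strata cannot be altered for those already enrolled.

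The article provides the means, through the full SAP to be uploaded before analysis and the registered, justified amendments under Protocol amendments. The choice should be made before any hospital imbalance has been seen, so that it cannot look data-driven.

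The cost is one degree of freedom in a model with about 34 to 43 expected non-RTW events, and at most about 1% in variance if the hospitals do not differ. No new data are needed and the planned sample size does not change. The gain is conditional balance, plus up to about 3 to 6% lower variance if the hospitals differ by 20 points.

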### Eligibility criteria

All adult survivors with first time out-of-hospital cardiac arrest who are discharged from the hospitals will be assessed eligible for inclusion. Survivors who, prior to the cardiac arrest, were part of the labour force with at least 2 years until they are qualified to receive retirement state pensions and who can understand and fulfil the study surveys (in Danish) are eligible for inclusion. Excluded are patients with short witnessed cardiac arrests with return of spontaneous circulation estimated less than 4 min and immediate awakening without ICU treatment.

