### Outcomes

#### Primary outcome

Data for the primary outcome will be obtained from the national register on social transfer payments (DREAM) [20]. The DREAM register is a prospective register based on data from the Ministry of Employment, the Danish Education Registers, the Danish Civil Registration System (CPR registry), and the Danish Tax Authority. The register contains all citizens in Denmark, who have received one or more social transfer payments in the period from 1991 until today. The type of transfer payment is registered on a weekly basis, and the register is updated monthly.

The primary outcome of the clinical trial is labour market participation, defined as a dichotomized outcome, employment vs. on social transfer payment 12 months after hospital discharge.

This measure has been proposed as adequate and relevant measure for assessing employment prognosis following intervention on a similar group of patients [21]. Furthermore, data will be obtained by questionnaire on the degree of workload and comparable work tasks compared to pre-cardiac arrest. Hence, labour market participation 12 months after hospital discharge (employment vs. social transfer benefits (DREAM)) and labour market participation during the 12 months after hospital discharge (DREAM) will be analysed.

Sequence analysis and a multistate model analysis will be used to visualize how survivors change states during the follow-up time and to assess influences from covariates on transitions between stages.

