### Primary outcome

The primary outcome will be analysed using logistic regression assessing RTW status at 12 months adjusting for the intervention and age at OHCA, sex, marital status, and occupation prior to OHCA. Patient-reported data on return-to-work will be used to enrich the analysis (e.g. self-employed persons, activation of substantial self-regulated pensions, unemployed without social transfer payment).

Sequence analysis will visualize how survivors change states during the follow-up time [43, 44] but also describe time spent in each state (working vs. social transfer benefit, etc.) and order of states during follow-up. However, sequence analysis is exploratory and cannot answer hypotheses or be adjusted for covariates.

Because return to work is complex, transitions between work states will be explored further. Multistate models can be used to assess influences from covariates on transitions between stages, e.g. from working to social transfer benefit, or reverse, or from working until death.

Retirement is an important state in this setting; however, retirement to private pensions is not registered in the DREAM database [20]. Thus, a multistate model including this important state will have to be built using data from survivors’ questionnaires. This is possible, as retirement is an absorbing state see (Supplemental Figure 1).

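### Entry wording does not exclude survivors already on a transfer payment before the arrest, and pre-arrest register status, the baseline value of the primary endpoint, is not named as a covariate or stratification factor

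*Protocol article*

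**What the plan says.** **Entry.** Eligibility criteria admits "Survivors who, prior to the cardiac arrest, were part of the labour force", provided that state pension age is at least 2 years away. The term is not defined and current employment is not required. The one stated exclusion concerns brief witnessed arrests with immediate awakening.

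**Endpoint.** Under Outcomes, Primary outcome, the endpoint is "labour market participation, defined as a dichotomized outcome, employment vs. on social transfer payment 12 months after hospital discharge". The Abstract and the statistical section call it RTW status. The source is the DREAM register, which covers citizens who have received at least one transfer payment since 1991. Of it the article says: "The type of transfer payment is registered on a weekly basis, and the register is updated monthly".

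**Model.** The statistical section Primary outcome specifies logistic regression "adjusting for the intervention and age at OHCA, sex, marital status, and occupation prior to OHCA". The Abstract and Table 2 list the same covariates. Randomisation is stratified on sex and age. Patient reports will supplement the register for named groups: "self-employed persons, activation of substantial self-regulated pensions, unemployed without social transfer payment". People on a transfer payment before the arrest are not among them.

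**The concern.** In ordinary usage the labour force includes unemployed job-seekers. A survivor who was on benefit before the arrest and still is at 12 months counts as a failure, although the arrest cost that person no work. The starting value of the endpoint can therefore differ between participants, and nothing named in the design or the primary model accounts for it.

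Other parts of the article presume a job to return to. The readiness scale has stages for people on full-time sick leave and for people working. The transitions in Table 3 start from sick leave or from work. The 71% planning rate is a return-to-work rate. The article also plans baseline adjustment for its repeated-measures models (section on checking assumptions), but not for the primary endpoint.

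At stake are power, the odds ratio's sensitivity to an uneven split of such participants between about 85 to 107 per arm, and what a return-to-work result means.

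**Working it through.** **1. The plan's own figure.** Sample size gives 71% vs 88.8%, 80% power and 85 per arm. Alpha is not stated; I assume two-sided 5%. On the log odds ratio scale without a margin:

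- OR = (0.888 × 0.29)/(0.112 × 0.71) = 3.24, ln OR = 1.175
- variance term = 1/(0.71 × 0.29) + 1/(0.888 × 0.112) = 4.857 + 10.055 = 14.91
- n = (1.960 + 0.842)² × 14.91 / 1.175² = 84.8, so 85; and 85/0.8 = 106.25, so 107

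The 85 does not reproduce with the stated 10-point margin (394 per arm, two-sided). That is a separate matter; no margin is used below.

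**2. Assumptions not in the documents.** A share u was on a transfer payment before the arrest. The rest follow 71% vs 88.8%. Employment at 12 months among those on transfer in the control arm is r.

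**3. Difference between arms.**

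- No effect in those on transfer: difference = (1 − u) × 17.8 points.
- Same odds ratio, 3.24: r = 15% becomes 36.4% (odds 0.176 × 3.24 = 0.571) and r = 30% becomes 58.1% (odds 0.429 × 3.24 = 1.388), gains of 21.4 and 28.1 points. Difference = (1 − u) × 17.8 + u × 21.4 (or 28.1).

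**4. Unadjusted power by formula, no effect in those on transfer.** Example with u = 10%, r = 20%:

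- rates 0.9 × 0.71 + 0.02 = 0.659 and 0.9 × 0.888 + 0.02 = 0.819
- ln OR = 0.852; SE = √[(4.450 + 6.752)/85] = 0.363
- 0.852/0.363 − 1.960 = 0.39, so power is 65%

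**5. Chance imbalance.** SD of the difference in share between arms = √[2u(1 − u)/85]. With r = 20%, an imbalance moves the risk difference by imbalance × (0.71 − 0.20).

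| u | Difference, no effect | Unadjusted power by formula (r 0–40%) | Difference, same OR (r 15–30%) | 1.96 SD of imbalance | Shift in risk difference |
|---|---|---|---|---|---|
| 5% | 16.9 | 72–74% | 18.0–18.3 | 6.6 points | 3.3 points |
| 10% | 16.0 | 63–67% | 18.2–18.8 | 9.0 points | 4.6 points |
| 20% | 14.2 | 49–54% | 18.5–19.9 | 12.0 points | 6.1 points |

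**6. With and without the covariate, by simulation.** Logistic regression, 85 per arm, u = 5–20%, r = 15–30%. With nobody on transfer, power is 83%. The formula in step 1 gives 80%; it is slightly conservative here.

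| Effect in those on transfer | Without covariate | With covariate |
|---|---|---|
| None | about 52–74% | about 62–79% |
| Same odds ratio | about 75–84% | about 83–89% |

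The covariate raised power in every scenario with such participants, by about 1 to 15 points.

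**The case against.** **Frequency.** The wording permits people on transfer payments to enter; it does not show that any do. This stands, so every power figure above is conditional on an assumed share.

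**The model may already capture it.** Occupation before the arrest could be coded with a not-working category, and such coding is normally left to the analysis plan. This stands in part: one cannot say that the model ignores pre-arrest employment. But the planned subgroups (blue vs white collar, manual vs non-manual) suggest job type, and the covariates, listed in three places, do not name transfer status.

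**The endpoint is labour market participation.** A prior job-seeker who is employed at 12 months is then a legitimate success. This stands, and argues against excluding such people. The mismatch is with the return-to-work label and the planning rate.

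**Large losses need a null effect.** The intervention includes work preparation and job-centre collaboration, so zero effect in those on transfer is the pessimistic end. This stands. Under the same odds ratio, unadjusted power is about 75–84% against 83%, so most of the loss in the first row of the last table comes from the null assumption.

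**The 71% may come from a similarly mixed population.** The article does not describe its employment mix. If it was mixed, there is no dilution relative to plan.

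**Bias.** A reader might infer that the odds ratio is systematically biased. The documents do not support that: randomisation balances pre-arrest status in expectation and leaves only chance imbalance.

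**Register completeness.** DREAM holds people who have received a transfer, so never-recipients are identified only by absence. This affects how the covariate is coded, not whether it can be built.

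**Conclusion.** The point holds in a limited form. The entry wording leaves room for survivors already on a transfer payment, and the endpoint's baseline value is not named in the stratification or the primary model. The result is avoidable loss of precision, exposure to chance imbalance and unclear interpretation of return to work.

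The size depends on an unknown share and an unknown effect in these participants. For 5–20% of them, unadjusted power ranges from about 52% (no effect in them) to about 84% (same odds ratio), against 83% with none. Adjustment gives about 62–89% over the same range. It does not restore the planned power where dilution is real.

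Two stronger conclusions are tempting and unsupported: that the trial is known to enrol many such people, and that pre-arrest status is the strongest predictor of the endpoint. The documents give no figure for either.

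**What to change.** In the statistical section Primary outcome, add pre-arrest DREAM status to the logistic model. One example is any transfer payment in the 4 weeks before the arrest (yes/no), with no DREAM record counted as no transfer. Pre-specify a supportive analysis restricted to participants without a pre-arrest transfer payment, the group for whom return to work has its plain meaning. State how occupation is coded and whether the labour-force criterion includes people on transfer payments.

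The cost is one more model parameter and one more analysis, from the register already to be linked. No new data or patients are needed and eligibility can stay as it is. The article's amendment route, through the trial registration, can record the change before the analysis.

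The covariate cannot remove dilution if the intervention does not work in this group; the supportive analysis would help to show that.
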